### Proposed sample size

Considering this longitudinal design, in the calculation of the sample, we considered a 0.25 effect size, an alpha level of 0.05, a desired statistical power of 0.8, five measures, and three research groups (i.e., control, online intervention, enhanced online intervention). To run a three-level cluster-randomized trial, previous analysis suggested 40 groups per group condition with 15 participants in each, measured at five different time points (see section “Definition of the hierarchical model”).

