#### Psychological self-report measures

##### Self-Regulation Processes towards Healthy Eating Questionnaire

An adapted version of *Self-Regulation for Health* scale [50] will be used to assess the SR processes towards healthy eating. This measure consists of nine statements regarding the participants’ self-regulation towards healthy eating (e.g., “I plan my meals. I think about what I’m going to eat and what it takes to prepare my meal”). Responses to the individual items are scored from 1 (never) to 5 (always) in a Likert-like scale and summed to create a composite score ranging from 9 to 45, with higher scores implying more self-regulation.

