### Statistical analysis plan

The effectiveness of the HEP-S intervention will be assessed using linear mixed-effect models. Specifically, we will assess the impact of interventions groups vs. control group on changes over time regarding the primary outcomes (e.g., healthy eating behavior, SR, self-efficacy towards healthy eating). For that, we will first examine within-intervention group differences (i.e., over time) followed by between-intervention group assessments at each time point. Differences between groups will be supported if the beta-weight parameter for the interaction between group and time are statistically significant.

Moreover, statistics descriptive analyses will be computed to describe all participants’ characteristics by using chi-square tests and independent tests to compare groups on the distributions according to sex, age group, BMI *Z*-score classification, and others. In addition, secondary outcomes will be analyzed by using similar models, comparing the three research groups. Also, these secondary repeated measures (e.g., satisfaction with the program) will be examined by conducting an analysis of covariance to explore interference with main outcomes. Finally, no interim analyses of the primary and secondary outcomes are planned to be included in this trial.

All analyses will be completed by using SPSS software (version 26), and *p* values below .05 will be considered statistically significant. The normality, homoscedasticity, and linearity of the residuals of each model will be examined to ensure that the assumptions of the models are met.

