### Definition of the hierarchical model

To evaluate the effectiveness of program, a three-level cluster-randomized trial is considered where classrooms are randomly assigned to treatment and control groups. Let *Y*_*tij*_ denote the response at time *t* for *i*th participant (*i* = 1,…, *n*_*j*_) in the *j*th group (*j* = 1, …, *J*), e.g., the *i*th student in the *j*th classroom. The three-level model for longitudinal experiments that involve clustered data is as follows:
1$$ \mathrm{Level}-1:\kern0.5em {Y}_{tij}={\uppi}_{0 ij}+{\uppi}_{1 ij}{T}_{tij}+{e}_{tij},\kern0.5em {e}_{tij}\sim N\left(0,{\sigma}_{et}^2\right) $$2$$ \mathrm{Level}-2:\kern0.5em {\displaystyle \begin{array}{l}{\pi}_{0ij}={\beta}_{00j}+{r}_{0 ij}\\ {}{\pi}_{1ij}={\beta}_{10j}+{r}_{1 ij},\end{array}} $$3$$ {\displaystyle \begin{array}{l}\mathrm{Level}-3:\kern0.5em \begin{array}{l}{\upbeta}_{00j}={\gamma}_{000}+{\gamma}_{001}{G}_j+{u}_{00j}\\ {}{\upbeta}_{10j}={\gamma}_{100}+{\gamma}_{101}{G}_j+{u}_{10j},\end{array}\\ {}\left[\begin{array}{l}{r}_{0 ij}\\ {}{r}_{1 ij}\end{array}\right]\sim N\left[\begin{array}{l}0\\ {}0\end{array}\right],\left[\begin{array}{ll}{\sigma}_{r0}^2& \\ {}0& {\sigma}_{r1}^2\end{array}\right],\left[\begin{array}{l}{u}_{00j}\\ {}{u}_{10j}\end{array}\right]\sim N\left[\begin{array}{l}0\\ {}0\end{array}\right],\left[\begin{array}{ll}{\sigma}_{u0}^2& \\ {}0& {\sigma}_{u1}^2\end{array}\right]\end{array}} $$

Substituting Eqs. 2 and 3 into Eq. 1, we have the mixed model of interest
4$$ {Y}_{tij}={\gamma}_{000}+{\gamma}_{00j}{G}_j+{u}_{00j}+{r}_{0 ij}+{\gamma}_{100}{T}_{tij}+{\gamma}_{101}{G}_j{T}_{tij}+{u}_{10j}{T}_{tij}+{r}_{1 ij}+{e}_{tij} $$

The lowest level variance component is represented by *e*_*tij*_, and the two level 2 variances are as follows: the variability in intercepts across subjects (*r*_*0ij*_) and the variability in slopes across students (*r*_*1ij*_) nested within classrooms. The level 3 variance components are as follows: the variability in intercepts across classrooms (*u*_*00j*_) and the variability in slopes across classrooms (*u*_*10j*_).

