As Heo et al. [54] and others (e.g., [55]) have indicated, the most important goal of a longitudinal intervention is to test whether there are differences between intervention groups with respect to their average growth rates. Applying the approach of these authors, the power to detect a specified treatment difference between average rates of change for the groups is defined as the probability of rejecting the null hypothesis of no treatment-by-linear-trend interaction *H*_0_: γ_101_ = 0, given that it is fact false (γ_101_ ≠ 0). This hypothesis can be tested with
5$$ {F}_o=\frac{{\hat{\gamma}}_{101}^2}{Var\left({\gamma}_{101}\right)}=\frac{\Delta^2\left[{N}_1{N}_2{N}_3 Var(T)\right]}{2\left(1-{\rho}_1\right){\sigma}^2{N}_1 Var(T){\sigma}_{u1}^2}, $$

where Δ is the effect standardized effect size at the last time point, *N*_1_ is the number of level 1 units (repeated measures) per student, *N*_2_ the number of level 2 units (students) per classroom, *N*_3_ the number of level 3 units (classroom) per treatment condition, *Var*(*T*) is the population variance of the time variable *T*, $$ {\upsigma}_{u1}^2 $$ is the three-level random slope variance, σ^2^ is the sum of the other variances, and *ρ*_1_ is the correlation between outcomes measures at different time points on the same student nested within classroom.

The power of the test statistic *F*_0_, denotes 1 − *β*, can be written as follows:
6$$ 1=\beta =\phi \left\{{\left\{\frac{\Delta }{\left({N}_1-1\right)}\left[\frac{\left[{N}_1{N}_2{N}_3 Var(T)\right]}{2\left(1-{\rho}_1\right){\sigma}^2{N}_1 Var(T){\tau}_s}\right]\right.}^{\frac{1}{2}}-{Z}_{1-\left(\alpha /2\right)}\right\}, $$

where τ_*s*_ is the ratio of the three-level random slope variance to the sum of the other variances, ϕ is the cumulative distribution function of a standard normal distribution, and *Z*_1 − (α/2)_ is the 100 (1 − *α*/2) percentile of the standard normal distribution for a bilateral test.

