Consider the following hypothetical values for three-level cluster-randomized trial design parameters: $$ {\upsigma}_e^2=0.5 $$, $$ {\upsigma}_{r0}^2=0.3 $$, $$ {\upsigma}_{r1}^2=0.0 $$, $$ {\upsigma}_{u0}^2=0.2 $$, and $$ {\upsigma}_{u1}^2=0.1 $$. Under the fixed slopes model, the correlation between the outcomes from different student nested within the same classroom is $$ {\uprho}_2={\upsigma}_{u0}^2/\left({\upsigma}_e^2+{\upsigma}_{r0}^2+{\upsigma}_{u0}^2\right)=0.2 $$, whereas the correlation between the outcomes measured at different time points on the same students nested within classrooms is $$ {\uprho}_1={\upsigma}_{r0}^2+{\upsigma}_{u0}^2/\left({\upsigma}_e^2+{\upsigma}_{r0}^2+{\upsigma}_{u0}^2\right)=0.5 $$. Further assumptions are as follows: (a) number of classrooms per treatment condition: *N*_3_ = 40; (b) average number of students per classroom: *N*_3_ = 15; (c) number of repeated measures per student: *N*_1_ = 5; (d) alpha significance level: *α* = 0.05; and (e) statistical power: 1 − *β* = 0.80.

Given design parameters and further assumptions, the minimum detectable effect size is 0.25. In our opinion, an effect size of Δ = .25 is a good first estimate of the smallest effect size of interest in psychological research, since it is not irrelevant and requires a considerable sample size to detect a treatment effect predicted by the researcher.

Finally, we consider that a study with 80% power is a properly powered study, despite several researchers (see, e.g., [56]) consider this a value rather low, as it entails a 20% chance of not finding a theoretically important finding.

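### The primary growth model fixes the intercept-slope covariance at zero for children and classrooms without justification, and the effect on the group-by-time test depends on an unstated time origin (minor)

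*Protocol article*

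**What the plan says.** The section Definition of the hierarchical model gives each child and each classroom a random intercept and a random slope on time. In Eq. 3 both 2 x 2 covariance matrices carry a printed 0 off the diagonal. The text below Eq. 4 matches this. It names the child intercept and slope variances, and then for classrooms: "The level 3 variance components are as follows: the variability in intercepts across classrooms", followed by the slope variance. No covariance is named at either level. Eq. 4 is presented as the model for judging effectiveness.

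The Statistical analysis plan section makes one coefficient decisive: "Differences between groups will be supported if the beta-weight parameter for the interaction between group and time are statistically significant", with the threshold that p "values below .05 will be considered statistically significant". The power formula is two-sided ("percentile of the standard normal distribution for a bilateral test").

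The coding of time is not stated. Eq. 6 divides the standardised effect at the last time point by N1 - 1. That fits unit steps from 0 at baseline to 4 at the fifth measurement, with no group difference at the start.

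The main scale outcomes are bounded sums. Self-regulation, for example, is "summed to create a composite score ranging from 9 to 45". The two self-efficacy scores run 9-45 and 17-85, and knowledge runs 15-75.

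**The concern.** A zero intercept-slope covariance is not a neutral default, because its meaning depends on where time is zero. Let the covariance be c and the slope variance s at one origin. Moving the origin k units later makes the covariance c + k·s. With the article's classroom slope variance of 0.1, a zero at baseline becomes 0 + 2 × 0.1 = 0.2 at the middle visit. The model therefore asserts independence at one particular visit, and the article neither names that visit nor defends the choice.

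With time counted from baseline, the restriction forces the variance between children and between classrooms to be smallest at baseline and to grow with time squared. With the article's values, the between-classroom variance goes from 0.2 to 0.2 + 0.1 × 16 = 1.8 at the last visit, a ninefold rise. Children or classes that start low and catch up cannot be represented. If they exist, the slope variance is misestimated, and so is the standard error of the deciding coefficient. The planned residual checks (normality, homoscedasticity, linearity) do not examine this part of the model.

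**Working it through.** **Inputs from the article.** Residual variance 0.5; child intercept and slope variances 0.3 and 0.0; classroom intercept and slope variances 0.2 and 0.1; five measurements; "number of classrooms per treatment condition: *N*_3_ = 40"; "average number of students per classroom: *N*_3_ = 15" (the symbol for students is evidently meant to be N2, as in Eq. 5); "we considered a 0.25 effect size, an alpha level of 0.05, a desired statistical power of 0.8".

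**Assumed.** Time coded 0 to 4; one intercept-slope correlation r applied at both levels; constant residual variance; complete data; a two-arm contrast. As a second case, slope variances of 0.01 (classroom) and 0.02 (child).

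**Step 1: the article's own figure.** With Var(T) = 2, ρ1 = 0.5, σ² = 1 and τ = 0.1, and with a plus sign between the two denominator terms of Eq. 6 (it is absent in the text as extracted):

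MDES = 4 × (1.960 + 0.842) × √{2 × [0.5 + 5 × 2 × 0.1] / (5 × 15 × 40 × 2)} = 4 × 2.802 × √(3/6000) = 0.2506.

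This reproduces 0.25 under the 0-4 coding. No intercept-slope covariance enters the formula, so the present point leaves that figure unchanged. Whether the slope term suits a classroom-level slope is a separate question.

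**Step 2: true standard error.** With complete balanced data, the slope difference has variance 2 × [s_class + s_child/15 + 0.5/(15 × 10)]/40, where 10 is the sum of squares of time about its mean. The covariance does not appear, so the estimate itself and its true precision are unaffected. What can go wrong is the standard error that the restricted model reports.

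- Article's variances: 2 × (0.1 + 0 + 0.00333)/40 = 0.00517, true SE 0.072.
- Assumed smaller variances: 2 × (0.01 + 0.00133 + 0.00333)/40 = 0.00073, true SE 0.027.

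**Step 3: reported standard error.** The zero-covariance model was fitted in large samples (the parameter values closest to the true covariance in Kullback-Leibler distance). Type I error is then 2[1 - Φ(1.96 × SE reported / SE true)].

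| r | Article's slope variances: SE ratio, type I | Assumed 0.01 and 0.02: SE ratio, type I |
|---|---|---|
| -0.7 | 0.971, 5.7% | 0.913, 7.4% |
| -0.5 | 0.980, 5.5% | 0.944, 6.4% |
| -0.3 | 0.988, 5.3% | 0.969, 5.7% |
| 0 | 1.000, 5.0% | 1.000, 5.0% |
| +0.3 | 1.011, 4.8% | 1.025, 4.4% |
| +0.5 | 1.018, 4.6% | 1.041, 4.1% |

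For example, at r = -0.5 in the last column: 2[1 - Φ(1.96 × 0.944)] = 2[1 - Φ(1.850)] = 6.4%. Simulated null trials (9,000 per setting, same assumed variances) gave 5.9%, 6.7% and 7.5% at r = -0.3, -0.5 and -0.7, against 5.1-5.3% with the covariance estimated.

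**Step 4: time origin.** With time centred at the middle visit, type I error is 5.0% at every r. If the residual variance differs by visit, as the subscript in Eq. 1 allows, it is at most 5.2%.

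**Step 5: do bounded scores produce the problem?** Scores were generated with zero covariance and clipped at a ceiling, with time 0-4. The trend is the common rise per visit, in baseline SD.

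| Ceiling above baseline mean | No trend | Trend 0.15 |
|---|---|---|
| 2 SD | 5.0-5.1% | 5.0-5.5% |
| 1 SD | 5.0-5.2% | 5.1-6.7% |
| 0.5 SD | 5.0-5.2% | 5.1-7.6% |

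With the article's own variances every ceiling case stays at 5.0-5.1%. The upper ends come from smaller assumed slope variances. With both covariances estimated, type I error is 5.0% throughout.

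**The case against.** A reader might infer that, because the outcomes are bounded, the standard error is too small and false positives will exceed 5%. The documents do not support that. They give no sign or value for any intercept-slope covariance, and nothing says that baseline scores lie near a bound; the questionnaire sections give only ranges. Step 5 shows that a ceiling matters only if scores sit close to it and also rise. The article does expect self-regulation, self-efficacy and knowledge to rise, so a negative covariance is possible, but it is not established.

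Other objections have force:

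- The larger figures rest on assumed slope variances. With the article's own values the excess is at most 0.7 percentage points at r = -0.7. Its child slope variance of 0.0 leaves no child-level covariance to restrict. Those values are themselves labelled hypothetical, however, and Eq. 3 keeps a child slope.
- If time is centred, the effect almost vanishes. The article does not say that it is centred, and Eq. 6 points to a baseline origin.
- The calculations take the classroom as the cluster, as the model does. The randomization section allocates schools, so the figures describe the written model and not type I error under school allocation.
- Outcome-dependent dropout in one arm would shift the last-visit difference by only about 0.01-0.03 SD, against a target of 0.25.
- Covariance structure is often left to a statistical analysis plan that is not shown here. That would answer a silence, but the article writes the zeros into the model.

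**Conclusion.** The restriction is real, explicit and unjustified, and its effect depends on a time origin that the text leaves unstated. With time from baseline, the deciding test can err in either direction. At correlations of -0.3 to -0.7, type I error is about 5.3-5.7% with the article's slope variances and about 5.7-7.5% with the smaller assumed ones (large-sample and simulated results together). At +0.3 to +0.5 it is about 4.1-4.8%. These figures assume equal correlations at both levels, complete data and time coded 0-4.

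It cannot be concluded that the trial's false-positive rate exceeds 5%, nor that bounded scores make this so. The severity is minor. The point is worth raising because the restriction bears on the primary test and is cheap to remove.

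**What to change.** In Eq. 3 replace both diagonal matrices with unstructured 2 x 2 matrices, so that the intercept-slope covariance is estimated for children and for classrooms (COVTYPE(UN) on each RANDOM statement in SPSS MIXED). Add the covariances to the list of components below Eq. 4. State how time is coded, including its origin and the spacing of the visits. State in advance that a covariance is dropped, with time centred, only if the model does not converge. If the investigators prefer to keep the zeros, they should justify them and name the time origin to which they apply.

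The cost is two extra parameters, a short syntax change and a small risk of non-convergence. That risk is greatest at child level if the child slope variance is close to the planning value of 0, where the correlation is barely identified; the fallback covers this. The stated detectable effect of 0.25 has no covariance term and is unchanged. The Trial status section says that recruitment had not begun at submission, so the change could be prespecified.

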**Methods:**

A three-armed randomized controlled trial will be conducted in several schools in Portugal. It will include a standard control group, with no intervention; an online intervention group, with the program for 20 weeks; and an enhanced online intervention group, with the program for 20 weeks embedded with gamification strategies throughout the program. Per research group, 40 groups of about 15 children each will be recruited and measured at five different time points. The three research groups will complete the same assessment protocol at the same timings (baseline, post-intervention, and 3, 6, and 9 months’ follow-ups). The assessment protocol will include anthropometric and psychological measures. The primary outcome measures will be the development of self-regulation skills for healthy eating over time, the development of self-efficacy attitudes, knowledge about healthy eating over time, and others. The secondary outcome measures will include the effect of gamification strategies, engagement, and satisfaction with the program, among others. The program will comprise the following: (i) a weekly group synchronous videoconference session with a trained educational psychologist serving as a mediator and (ii) a weekly parental involvement activity. Narratives, or story-tools, embedded with self-regulation strategies are at the core of the intervention.

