### Goals and expected outcomes

The main purpose of this study is to evaluate the efficacy of an online intervention, narrative-based with or without gamification strategies, designed to promote healthy eating by fostering the use of SR strategies among elementary school-aged children. Thus, the major goals are to promote children’s use of SR strategies for healthy eating, to strengthen their sense of self-efficacy regarding healthy eating, and to increase the consumption of healthy foods. Other goals of the study include the following: increase knowledge about healthy eating and consequences of unhealthy nutrition or lifestyle; contribute to healthier food preferences; and contribute to more positive attitudes and perceptions about healthy eating. Thus, we want to assess the feasibility of conducting an online intervention with this population and examine the advantages of embedding the program with gamification strategies, by comparing it to the program without these strategies.

Overall, it is expected that children taking part of the intervention will, at the end of the intervention, increase their use of SR strategies for healthy eating, enhance their sense of self-efficacy for healthy eating, and increase their consumption of healthy foods. Additionally, it is expected that their knowledge on the topic will increase, that their food preferences become healthier, and that they will display perceptions and attitudes about the topic that are more positive. Lastly, it is expected that participants enrolled in the enhanced-online-intervention group will be more engaged in the intervention than the online-intervention group.

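### The stated criterion for a group difference is a linear trend across the follow-ups, which gives the end-of-program visit a negative weight although the gain is expected at that visit

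*Protocol article*

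**What the plan says.** Under Goals and expected outcomes, the protocol article states when the benefit should appear: children will, "at the end of the intervention, increase their use of SR strategies for healthy eating". The program lasts 20 weeks, so this is the final assessment, T1. All later visits follow the end of the program.

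The Statistical analysis plan section gives the criterion: "Differences between groups will be supported if the beta-weight parameter for the interaction between group and time are statistically significant". Just before that, it plans an examination of change within groups, "followed by between-intervention group assessments at each time point".

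Definition of the hierarchical model presents the model for evaluating effectiveness. Eqs. 1 to 4 contain one numeric time term T and one group-by-T coefficient, γ101. The section says the main aim of a longitudinal intervention is "to test whether there are differences between intervention groups with respect to their average growth rates", sets H0: γ101 = 0, and defines power as "the probability of rejecting the null hypothesis of no treatment-by-linear-trend interaction". The effect size Δ is "the effect standardized effect size at the last time point", and Eq. 6 divides it by N1 − 1.

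The number of visits is not settled. The abstract lists five ("baseline, post-intervention, and 3, 6, and 9 months" follow-ups), and Proposed sample size also uses five. Table 3, Anthropometric measures, and Primary and secondary outcome measures give four, ending at 6 months.

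**The concern.** Dividing Δ at the last visit by N1 − 1 describes a benefit that starts at zero and grows by the same amount at every visit, including the months after the program has stopped. No section predicts that shape. The Goals section points to a gain that is already present at T1 and is then kept or partly lost.

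A single straight line fits that shape poorly. T1 lies in the early half of the time axis, so a benefit there pulls the estimated slope difference down. Part of the benefit goes instead into the group difference at T = 0 (γ001), which is not tested. A real effect at program end could then fail the stated criterion, and even a fully maintained effect would be tested with less power than stated.

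**Working it through.** **Inputs.** N1 = 5 visits, N2 = 15 students, N3 = 40 classrooms per arm, two-sided α = 0.05, Δ = 0.25, ρ1 = 0.5, and slope-variance ratio τs = 0.1 (0.1 divided by 0.5 + 0.3 + 0.2). All come from Definition of the hierarchical model. With T = 0 to 4, Var(T) = 2.

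**1. The plan's own figure.** The general form is power = Φ{[Δ/(N1 − 1)] × √[N1·N2·N3·Var(T)/D] − 1.96}, with N1·N2·N3·Var(T) = 5 × 15 × 40 × 2 = 6000.
- Eq. 6 as printed has a product in the denominator: D = 2 × 0.5 × 1 × 5 × 2 × 0.1 = 1. The minimum detectable effect is then (1.96 + 0.842) × 4/√6000 = 0.145, not 0.25.
- With a sum, D = 2[(1 − ρ1) + N1·Var(T)·τs] = 2(0.5 + 1.0) = 3. The standard error of the slope difference is 1/√(6000/3) = 0.02236. The minimum detectable effect is 2.802 × 4 × 0.02236 = 0.2506, and power at 0.25 is Φ(0.0625/0.02236 − 1.96) = 0.798. This reproduces the stated 0.25 and is used below.

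**2. Weight of each visit in the slope.** The weight is (t − mean t)/Σ(t − mean t)². For complete data with constant residual variance, generalised least squares under the plan's random intercept and slope gives the same weights.

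| Schedule and coding | Centred times | T1 |
|---|---|---|
| Five visits, index | −2, −1, 0, 1, 2 | −1 |
| Four visits, index | −1.5, −0.5, 0.5, 1.5 | −0.5 |
| Five visits, months (0, 4.6, 7.6, 10.6, 13.6) | −7.28, −2.68, 0.32, 3.32, 6.32 | −2.68 |
| Four visits, months (0, 4.6, 7.6, 10.6) | −5.7, −1.1, 1.9, 4.9 | −1.1 |

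The T1 weight is negative in all four.

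**3. A 0.25 SD gain at T1, five visits by index (Σ = 10).**
- Fully maintained: slope = 0.25 × (−1 + 0 + 1 + 2)/10 = 0.05. The implied end effect is 4 × 0.05 = 0.20. Power = Φ(0.05/0.02236 − 1.96) = Φ(0.276) = 0.61. The fitted group difference at T = 0 is 0.20 − 2 × 0.05 = 0.10, although the true difference there is zero.
- Fading 100/75/50/25%: slope = 0.25 × (−1 + 0 + 0.5 + 0.5)/10 = 0. The chance of a significant benefit is 0.025. The average gain of 0.125 goes entirely into γ001.
- Gone by 3 months: slope = 0.25 × (−1)/10 = −0.025, an implied end effect of −0.10.

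**4. Four visits by index (Σ = 5).**
- Fully maintained: slope = 0.25 × (−0.5 + 0.5 + 1.5)/5 = 0.075; end effect 3 × 0.075 = 0.225. With the same form of D, N1·N2·N3·Var(T) = 4 × 15 × 40 × 1.25 = 3000 and D = 2(0.5 + 0.5) = 2, so √1500 = 38.73. Power is Φ(0.0833 × 38.73 − 1.96) = 0.90 for the growing gain and Φ(0.075 × 38.73 − 1.96) = 0.83 for the maintained one.
- Fading 100/67/33%: slope = 0.25 × (−0.5 + 0.333 + 0.5)/5 = 0.0167; end effect 0.05, which is 20% of 0.25.
- Fading 100/50/0%: slope = 0.25 × (−0.5 + 0.25 + 0)/5 = −0.0125, negative.

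**5. Month coding, five visits.** Fully maintained gives an end effect of 0.2225. Fading 100/75/50/25% leaves a small positive slope (end effect 0.024). Halving at each visit gives a negative one (−0.0275).

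**The case against.** The quoted definition of power comes from the sample-size argument, and the sentence with the criterion does not itself say that time is linear. Coding of time is often left to an analysis plan, which is not shown here. That would settle the matter if the model were left open. But the hierarchical model section says it serves to evaluate effectiveness, and Eqs. 1 to 4, H0 and Var(T) all fix one numeric trend.

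Between-group comparisons at each visit are already planned, and the primary outcomes are defined across all assessments. A gain at T1 would therefore be estimated and visible. This stands. What is missing is any rule that lets that comparison decide when the trend is null.

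The plan also checks linearity of residuals, which might reveal a step followed by decay. No consequence is stated, so this is only a partial safeguard.

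The article shows interest in growth rates and in sustained change, and no section predicts fading. This stands too: a test that gives little credit to a vanishing effect is arguable. But a slope does not measure maintenance either, since it loses power for a gain that is perfectly kept and rewards one that emerges late.

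A reader might infer that the trial would declare a working program harmful. The documents do not support that. A negative slope needs marked fading, more of it with four visits than with five, and the planned visit comparisons would show the early gain. A reader might also take 80% and 61% as results of Eq. 6. As printed, Eq. 6 gives 99.8% at 0.25 and, for an end effect of 0.20, Φ(0.05 × √6000 − 1.96) = 97%.

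**Conclusion.** The concern holds as a mismatch between the stated criterion and the stated expectation, and it should be fixed. The sign of the T1 weight does not depend on the visit schedule or time coding, given complete data and constant residual variance. Eq. 1 lets residual variance differ by visit, and missing visits would also change the weights.

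The size does depend on the schedule. A fully maintained 0.25 SD gain is read as 0.20 with five index-coded visits and 0.225 with four. Power falls from about 80% to 61% with five visits, and from 90% to 83% with four. These power figures rest on the denominator that reproduces 0.25. That denominator omits N2 from the slope-variance term, although the section places this variance at classroom level, so they show the relative loss and are not a forecast. The zero and negative slopes are possible outcomes under assumed fading profiles; the documents do not say that the effect will fade.

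**What to change.** Enter visit as a categorical factor with a group-by-visit interaction, and either adjust for baseline or constrain the baseline means to be equal across arms. Make the between-arm contrast at T1, which is already among the planned comparisons, the deciding test, in line with the Goals section. Report the follow-up contrasts as maintenance, and keep the linear trend as exploratory. Settle whether there are four or five visits.

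Restate the power for the chosen contrast. As a guide, for a simple T0-to-T1 change in one pairwise comparison with a 0.25 SD gain, the variance is 2[2 × 0.5/600 + v], where 600 = 15 × 40 students per arm. If the slope variance acts at student level, v = 0.1/600 and power is 98%. If it acts at classroom level, v = 0.1/40 and power is Φ(0.25/√0.00833 − 1.96) = 78%. The restated figure could therefore be slightly less favourable than 80%.

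The cost is a change of wording, a new power calculation and a few more fixed-effect parameters. No new data are needed. The article reports that recruitment had not begun at submission, so the change could have been prespecified then.

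### The detectable effect of 0.25 is labelled a standardized effect at the last time point, but it is scaled by an SD without slope variance and needs re-deriving with the slope carried at classroom level

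*Protocol article*

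**What the plan says.** All of this is in the protocol article, section Definition of the hierarchical model.

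- **Effect size.** Under Eq. 5, Δ "is the effect standardized effect size at the last time point". The SD that standardizes it is not named.
- **Scaling variance.** The same sentence says that σ² "is the sum of the other variances, and" so leaves the classroom slope variance out. Eq. 6 divides Δ by N1 − 1 and scales by this σ².
- **Level of the slope.** The level 3 components include "the variability in slopes across classrooms".
- **Inputs.** Residual variance 0.5, student intercept 0.3, student slope 0.0, classroom intercept 0.2, classroom slope 0.1. There are 40 classrooms per condition, 15 students per classroom and 5 measures, with two-sided α 0.05 and power 0.80.
- **Correlations.** ρ2 = 0.2 and ρ1 = 0.5 are given for a model without random slopes: "Under the fixed slopes model, the correlation between the outcomes from different student nested within the same classroom".
- **Result.** "Given design parameters and further assumptions, the minimum detectable effect size is 0.25". The text then adopts 0.25 as a first estimate of the smallest effect of interest, and the section Proposed sample size relies on the same value.

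**The concern.** A reader takes a standardized effect at the last time point to be expressed in SDs of the outcome at that visit. The plan's model has random classroom slopes, so the outcome variance grows over time, yet σ² contains no slope variance. The 0.25 and its label then refer to different scales. The same inputs also imply a classroom correlation at the last visit that the article never shows.

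The whole sample-size argument rests on 0.25 being both detectable and worth detecting. If the scale is unclear, and the formula behind the figure does not match the stated model, a reader cannot tell what the trial can detect.

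**Working it through.** **Inputs.** σ² = 0.5 + 0.3 + 0.2 + 0.0 = 1.0. ρ1 = (0.3 + 0.2)/1.0 = 0.5, so (1 − ρ1)σ² = 0.5. The ratio τs is 0.1/1.0 = 0.1. N1 = 5, N2 = 15, N3 = 40. Five unit-spaced times give Var(T) = 2, so N1·N2·N3·Var(T) = 5 × 15 × 40 × 2 = 6000. z-sum = 1.960 + 0.842 = 2.802.

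**1. Reproduce 0.25.** Detectable Δ = 2.802 × (N1 − 1) × SE of the slope difference.

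- Denominator as a sum: 2 × (0.5 + 5 × 2 × 0.1) = 3.0. SE = √(3.0/6000) = 0.02236. Δ = 2.802 × 4 × 0.02236 = **0.2506**. Power at 0.25 = Φ(0.0625/0.02236 − 1.96) = 0.798. This matches.
- Denominator as printed in Eq. 6 (a product): 2 × 0.5 × 5 × 2 × 0.1 = 1.0. Power at 0.25 = 0.998 and detectable Δ = 0.145. This does not match.
- Fixed slopes: 2 × 0.5 = 1.0, the same 0.998. This does not match.

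So 0.25 needs the sum, a non-zero slope term and σ = 1.

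**2. Scale at the last visit.** Dividing Δ by N1 − 1 turns a last-visit effect into a slope when time starts at 0 in unit steps. On T = 0 to 4, variance at T = 1.0 + 0.1T², and classroom correlation = (0.2 + 0.1T²)/(1.0 + 0.1T²).

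| T | Variance | SD | 0.25/SD | Classroom correlation |
|---|---|---|---|---|
| 0 | 1.0 | 1.00 | 0.250 | 0.20 |
| 1 | 1.1 | 1.05 | 0.238 | 0.27 |
| 2 | 1.4 | 1.18 | 0.211 | 0.43 |
| 3 | 1.9 | 1.38 | 0.181 | 0.58 |
| 4 | 2.6 | 1.61 | **0.155** | **0.69** |

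**3. Carry the slope variance at the level the plan gives it.** Under the plan's three-level model with no student slope variance, one classroom's mean slope has variance 0.1 + 0.5/(N1·N2·Var(T)) = 0.1 + 0.5/150 = 0.1033. The difference between two arms of 40 classrooms has variance 2/40 × 0.1033 = 0.005167. Equivalently, it is 2 × (0.5 + 15 × 10 × 0.1)/6000 = 31/6000. The factor N2 = 15 in the slope term is what step 1 lacks.

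- SE = 0.0719.
- Detectable Δ = 2.802 × 4 × 0.0719 = **0.81σ**, or 0.81/1.61 = **0.50 last-visit SD**.
- Power at 0.25σ = Φ(0.0625/0.0719 − 1.96) = **0.14**.
- A true 0.25 last-visit SD is 0.25 × 1.612 = 0.403σ. Power is then 0.29, against 0.995 from the step 1 formula.

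**4. Sensitivity to the slope variance, for illustration.** These values are assumptions and do not come from the article.

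- 0.005: slope term 15 × 10 × 0.005 = 0.75; SE = √(2 × 1.25/6000) = 0.0204; detectable Δ = 0.23σ. Last-visit classroom correlation = 0.28/1.08 = 0.26.
- 0.01: slope term 1.5; SE = √(2 × 2.0/6000) = 0.0258; detectable Δ = 0.29σ. Correlation = 0.36/1.16 = 0.31.

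**The case against.** **The label says when, not which SD.** The definition places the effect at the last visit without naming a divisor, σ² openly excludes slope variance, and 0.25 reproduces. Much of this stands: scaling by an SD without slope variance is a usable convention once labelled, and the 0.25 is not an arithmetic slip. What remains is that, read plainly, the definition promises a last-visit effect and the number is not one.

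**The time coding is inferred.** This stands. Any unit-step coding gives 0.2506, because only N1 − 1 and Var(T) enter. Centred time would give 0.211 SD and a correlation of 0.43; T = 1 to 5 would give 0.25/√3.5 = 0.134 and 2.7/3.5 = 0.77. With the four assessments in Table 3, coded 0 to 3, the values are 0.181 and 0.58. None returns 0.25 with 0.20. The 0.81σ in step 3 does not depend on the time origin.

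**The fixed-slopes correlations.** A reader might infer that they corrupt the power figure. They do not: (1 − ρ1)σ² is simply the residual variance of 0.5, and ρ2 is not in the formula. Nor does 0.69 contradict a stated value, since the article limits 0.20 to the fixed-slopes model. The 0.69 is only what the inputs imply.

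**Two readings of the 0.1.** If 0.1 were a student-level slope variance, step 1 would be appropriate and the last-visit classroom correlation would be 0.2/2.6 = 0.08. But the article assigns 0.1 to classrooms and sets the student slope variance to 0.0.

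**The inputs are called hypothetical.** True, and the article gives no benchmark for a plausible last-visit correlation. That 0.69 is too high is a judgement for the authors.

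**Conclusion.** The point holds as a mismatch between label, formula and model. The 0.25 is in units of σ = 1; on time coded 0 to 4 it is 0.155 SD at the visit the definition names. With the slope variance carried at classroom level, the printed inputs support a detectable effect of about 0.81σ (0.50 last-visit SD), not 0.25, and about 14% power at 0.25.

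A reader might infer from the 0.155 that the trial is more sensitive than claimed, or that a true 0.25 last-visit SD would be found with 99% power. The documents do not support this: both figures keep the formula that omits N2, and with N2 included power at that effect is 29%. The scaling mismatch alone does not show lost power; the shortfall comes from the level at which the slope variance enters.

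These figures assume five unit-spaced visits, equal classrooms of 15, complete data and the printed variances. The last-visit values also assume time zero at baseline.

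**What to change.** In the section Definition of the hierarchical model:

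1. State the time coding and the SD that standardizes Δ.
2. Correct the denominators of Eqs. 5 and 6 to a sum, with N2 in the slope term, and derive the detectable effect from the plan's own random-slopes model. On the present inputs, report about 0.81σ (0.50 last-visit SD). Do not print 0.155 or 99% power.
3. Show the implied last-visit classroom correlation. If 0.69 is not intended, justify another slope variance and restate the detectable effect from it. As illustrated above, 0.005 to 0.01 gives 0.23 to 0.29σ.
4. Carry the restated figure into the section Proposed sample size.

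The cost is one recalculation and some rewording. The correction changes the stated figure; the number of children need not change.
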